#### Secondary outcome

Symptoms of anxiety will be measured using the *Generalized Anxiety Disorder-7* (GAD-7) [28], a self-report measure of the extent to which respondents have been bothered by 7 symptoms of generalized anxiety, corresponding to the DSM-IV criteria, over the past 2 weeks using a 4-point Likert scale from 0 “not at all” to 3 “nearly every day.” The sum scores range from 0 to 21 with scores of ≥ 5, ≥ 10, and ≥ 15, representing mild, moderate, and severe levels of anxiety, respectively. Psychometric properties of the GAD-7 are well documented [29].

#### Pertinent demographics measures

A demographics questionnaire was designed to measure *sex* (male/female), *age* (in years), *race*, *ethnicity*, self-reported *physical and mental health conditions*, *marital status*, and having *children living at home*. To capture work-related characteristics that may relate to stress, we will measure *bi-vocational status* (i.e., job in addition to serving as clergy) and *clergy appointment*, i.e., whether they serve in a church or not.

#### Additional measures

Physical activity levels will be measured using the *Godin-Shephard Leisure-Time Physical Activity Questionnaire* [30], a self-report measure of how often in the past 7 days and for how many minutes per time one has engaged in physical activity, measured separately for strenuous, moderate, and mild exercise. We will use self-reported weight and height to assess *body mass index* [31]. We will use single items to assess average daily *caffeine intake*, average weekly *alcohol consumption*, *financial stress* (how stressful is your current financial situation for you? not at all-extremely), *number of hours worked* per week, and *preference for online vs in-person intervention*. *Depressive symptoms* will be measured using the self-report eight-item Patient Health Questionnaire (PHQ-8) which asks about the frequency of specific depressive symptoms experienced within the past two weeks [32, 33].

### Timeline of assessments

#### Surveys

Participants will complete the study measures immediately before starting the intervention (baseline), 12 weeks after commencing the intervention, and 24 weeks after commencing the intervention (see Fig. 2). Participants will be prompted to complete the surveys via email and given a link to an online survey whose data are securely stored in REDCap. The data collection window will be from 1 week prior to 3 weeks after the time point.

**Fig. 2 Fig2:**
[figure not shown]
Timeline of measures: surveys, ECG, and daily practice times (reported via text messaging)

#### Texting

Participants will receive daily text messages at noon that inquire their practice from the previous day. In the case of stress proofing, the text asks how many daily resets were performed; for MBSR, the number of minutes of formal meditation practiced; and for the Daily Examen, whether they have prayed the Examen prayer or not. Participants who have not responded by 4 p.m. will receive a reminder. Text messages will be distributed through an automated system generated by programmers at Duke Digital Health.

#### Qualitative interviews

Purposive samples of participants from each intervention group will be invited to participate in in-depth interviews about their experiences. Interviews will be performed between 5 and 15 weeks after starting the intervention with the goal of evaluating acceptability, perceived value, benefits, unintended consequences, and intervention delivery. We will select up to three participants in early workshop groups as we refine the intervention delivery and 1–2 participants in later workshop groups. Participants will be selected using their text message engagement data, to include both high- and low-practice participants. Interviews will be conducted using semi-structured interview guides and audio-recorded. The interviewer will take comprehensive notes and complete a post-interview debrief form. Interview notes will be coded in qualitative software using a pre-defined book of index codes [34]. Content analysis will be conducted to achieve the goals stated above.

### Participant engagement

Participant engagement will be encouraged through multiple methods. Participants will acknowledge their understanding of the three core aspects of participation (workshop attendance, surveys, and heart rate tracking), and commit to participate in all aspects. Second, participants will be oriented to the study as they prepare to begin their intervention (or ask questions via phone, email, or Zoom for controls). At this time, participants are given program materials and study-branded items such as coffee mugs, water bottles, and pens, plus information about the compensation for completing each of three surveys and two occasions of heart rate tracking. Course instructors and the research team will contact participants via email to remind them of upcoming class sessions and surveys. Participants will have the opportunity to engage further with their instructors in online follow-up sessions (2 weeks and 6 weeks for DE; 1 month for SP). The daily text message to collect the amount of practice also serves as a daily engagement prompt. Lastly, the participants will receive “thank you” correspondence in the mail prior to being invited to complete their final survey.

### Analysis

#### Statistical analysis plan

##### Power analysis

A baseline average C-SOSI score of 0.92 (SD = 0.46) and average 12-week follow-up scores of 0.7 (SD = 0.58) for MBSR, 0.55 (SD = 0.36) for stress proofing, and 0.51 (SD = 0.38) for Daily Examen are expected based on study pilot data. Given an alpha of 0.0167 (based on a Bonferroni correction to hypothesis tests for the effects of 3 interventions on C-SOSI scores), a per-arm sample size of 195 for MBSR, 40 for Daily Examen, and 47 for stress proofing will yield 80% power to detect a between-arm difference in the means at 12 weeks of 0.22 for MBSR, 0.37 for stress proofing, and 0.41 for Daily Examen for a two-sample *t*-test with unequal variances, allowing for a loss-to-follow-up of 20% and a design effect of 1.3 (corresponding to an ICC of 0.027 and average cluster size of 12) to account for clustering caused by the group-based intervention delivery.

Previous literature recommends that medium effect size (difference in means/standard deviation) for HRV be defined as 0.50. A per-arm sample size of 140 will yield 80% power to detect an effect size of 0.50 for a two-sample *t*-test with an alpha of 0.0167, allowing for a loss-to-follow-up of 20% and a design effect of 1.3 to account for the group-based intervention delivery. All power analyses were performed using the PASS 2021 software.

##### Data analysis

All primary and secondary study outcomes are measured on continuous scales and will be reported with mean estimates and 95% confidence intervals using the intention-to-treat principle with reference to the waitlist vs non-waitlist for participants randomly assigned prior to March 1, 2020. Linear mixed models will be specified with fixed effects for time and intervention status, and partially clustered random effects for the non-waitlist arms will be used to account for the clustering caused by workshop-level intervention delivery that affects participants in the intervention condition vs the un-clustered structure for those in the waitlist condition. Distributions of residuals will be examined to confirm that modeling assumptions are met. Models with adjusted and unadjusted estimates will be specified, with adjustment covariates such as age, sex, and bi-vocational status chosen prior to unblinding and finalization of the analysis plan and sensitivity analyses to include any additional relevant covariates that are identified. We will include race and ethnicity contingent upon there being meaningful heterogeneity. We may choose to adjust for baseline stress level to improve the precision of the treatment effect. In addition, for the models evaluating HRV, an a priori decision was made to include baseline sex, age, caffeine intake, alcohol consumption, body mass index, and physical activity as covariates given the influence that these variables exert on HRV [35]. For the primary outcome of stress symptoms, *p*-values will be calculated for the 12-week differences for each of the 3 interventions vs waitlist and will be adjusted for multiple comparisons using the Benjamini-Hochberg correction [36].

The effects of preferences on intervention estimates will be ascertained by introducing binary indicators for receipt of intervention preference vs assignment by random choice, which will be interacted with intervention indicators. Because this study is not powered to detect such interaction effects, the analytic focus will be on the magnitude of interaction effects and their 95% confidence intervals.

We will perform sensitivity analyses adjusting for any influential covariates (e.g., baseline financial stress, depressive symptoms, marital status; see Table 2) that are imbalanced by chance between waitlist and non-waitlist arms.

Due to the effects of the COVID-19 pandemic on recruitment, intervention delivery, and potential follow-up rates, analyses will be approached from two angles. First, analyses will be performed using data from participants recruited prior to March 1, 2020, when the randomized-waitlist design was applied. Standard analytic approaches applicable to randomized studies and CONSORT reporting will be applied. Second, participants recruited prior to March 1, 2020, will be pooled with those recruited after March 1, 2020, and data will be analyzed with methods appropriate to observational study designs using as-treated methods (e.g., propensity score weighting to account for treatment selection).

If 5% or more of participants miss follow-up data, a sensitivity analysis will be performed using propensity score or multiple imputation methods to account for potentially informative missingness, and estimates will be compared to the original complete case estimates.

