**Methods and analysis:**

The overall design is a preference-based randomized waitlist control trial. United Methodist clergy in North Carolina will be eligible to participate. The intervention and waitlist control groups will be recruited by email. The interventions offered are specifically targeted to clergy preference and include mindfulness-based stress reduction, Daily Examen, and stress inoculation training. Surveys will be conducted at 0, 12, and 24 weeks with heart rate data collected at 0 and 12 weeks. The primary outcomes for this study are self-reported symptoms of stress and heart rate at week 12 for each intervention compared to waitlist control; the secondary outcome is symptoms of anxiety comparing each intervention vs waitlist control.

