## Methods

### Research objectives

#### Objective 1

To compare the impact of, separately, MBSR, the Daily Examen, and stress proofing with a waitlist control condition, on stress outcomes at 12 weeks.

Hypotheses 1 and 2: When randomly assigned to waitlist vs non-waitlist, MBSR, the Daily Examen, and/or stress proofing will be superior to the waitlist control on stress symptoms (hypothesis 1) and HRV (hypothesis 2) at 12 weeks (co-primary outcomes).

#### Objective 2

To compare the impact of, separately, MBSR, the Daily Examen, and stress proofing with a waitlist control condition, on anxiety symptoms at 12 weeks.

Hypothesis 3: When randomly assigned to waitlist vs non-waitlist, MBSR, the Daily Examen, and/or stress proofing will be superior to the waitlist control on anxiety symptoms at 12 weeks (secondary outcome).

#### Objective 3

To compare the impact of, separately, MBSR, the Daily Examen, and stress proofing with a waitlist control condition, on stress and anxiety symptoms at 24 weeks.

Hypotheses 4 and 5: When randomly assigned to waitlist vs non-waitlist, MBSR, the Daily Examen, and/or stress proofing will be superior to the waitlist control on stress symptoms (hypothesis 4) and anxiety symptoms (hypothesis 5) at 24 weeks (exploratory outcomes).

#### Objective 4

To determine whether having a preference, and that preference being honored, was associated with better outcomes on stress symptoms, HRV, and anxiety symptoms.

Hypotheses 6–8: Participants who had a stated preference and received that intervention (i.e., MBSR, the Daily Examen, and stress proofing combined) will experience larger between-arm (waitlist vs non-waitlist) differences in improvements on stress symptoms (hypothesis 6), HRV (hypothesis 7), and anxiety symptoms (hypothesis 8) at 12 weeks when compared to no-preference participants randomly assigned across interventions and waitlist (exploratory outcomes).

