#### Study arms: non-waitlist interventions and waitlist

This trial includes three non-waitlist study arms (mindfulness-based stress reduction, Daily Examen, and stress proofing) and one waitlist arm that includes two conditions: first providing control data and then participating in any intervention condition. Originally, participants were to be trained in small workshop formats delivered across NC between April 2020 and May 2021. Due to the global pandemic, all workshops were converted to online delivery formats and delivered during the same anticipated months. Interventions will be delivered in small groups of 10–25 participants. Survey data will be collected online, and HRV data will be collected by the participants in their respective personal settings.

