#### Heart rate

A subset of participants will be provided with an ambulatory heart rate monitoring device to wear for a 48-h period during week 0 and week 12, during which time participants proceeded with their usual daily routines, including exercising, bathing, and sleep activities.

Heart rate will be measured using continuous electrocardiographic (ECG) recording sampled at a rate of 1000 Hz and used to calculate *heart rate variability*. Participants will be fitted with an eMotion Faros 180 ambulatory heart rate recording device (Bittium) connected by electrode leads to two pre-gelled (Ag/AgCl) disposable Ambu BlueSensor wet-gel ECG electrodes attached beneath the right clavicle and left ribcage. The 48-h ECG recording will be imported to the Kubios HRV Premium V3.4.1 software [24], partitioned into 5-min segments, visually inspected to allow for manual correction of ectopic beats, detrended, and subject to Kubios’ automatic artifact correction algorithm [25]. Heart rate variability will be indexed using the time-domain metric *root mean square of successive RR differences* (*RMSSD*) given that it is less affected by breathing and a better suitable outcome measure in ambulatory studies than frequency-domain measures [26].

Following recommendations for the detection of circadian rhythmicity [27], 5-min segments across 24 h of recording will be subject to a cosinor analysis using the Cosinor package for R. Two individual-level cosine function parameters will be estimated by linear models with ordinary least square estimations to quantify the circadian variability parameters: (i) midline estimating statistic of rhythm (MESOR), defined as the rhythm adjusted 24-h mean, and (ii) amplitude, defined as the distance between MESOR and the maximum of the cosine curve (i.e., half the extent of rhythmic change in a cycle).

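### HRV is sized at alpha 0.0167, but the stated multiplicity correction covers stress only, and neither of the two HRV parameters is named as primary

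*Protocol article*

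**What the plan says.** All references are to the protocol article.

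- **Research objectives, Objective 1.** The hypothesis is that "MBSR, the Daily Examen, and/or stress proofing will be superior to the waitlist control on stress symptoms (hypothesis 1) and HRV (hypothesis 2"). The two outcomes are labelled together: "hypothesis 1) and HRV (hypothesis 2) at 12 weeks (co-primary outcomes"). They are numbered as separate hypotheses, and the and/or wording lets any one intervention support a claim.
- **Power analysis.** The stress comparison uses alpha 0.0167, explained as a Bonferroni correction for three interventions. The HRV comparison is 140 per arm for 80% power at an effect size of 0.50, "with an alpha of 0.0167, allowing for a loss-to-follow-up of 20% and a design effect of 1.3 to account for the group-based intervention delivery".
- **Data analysis.** For stress symptoms, p-values are to be calculated "for the 12-week differences for each of the 3 interventions vs waitlist and will be adjusted for multiple comparisons using the Benjamini-Hochberg correction". For HRV the section lists covariates but no multiplicity rule. All primary and secondary outcomes are to be reported with 95% intervals.
- **Heart rate.** HRV is indexed by RMSSD, which then enters a cosinor analysis: "Two individual-level cosine function parameters will be estimated by linear models with ordinary least square estimations". These are the MESOR and the amplitude. Neither is designated as the primary endpoint.
- **Study arms.** The trial has "three non-waitlist study arms (mindfulness-based stress reduction, Daily Examen, and stress proofing) and one waitlist arm".

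**The concern.** The sample size section and the analysis section apply different rules to the same co-primary outcome. HRV was sized as though each of its three contrasts would be tested at 0.0167. The analysis text then restricts the correction, by name, to the other co-primary. An analyst who follows that text literally would test each HRV contrast at 0.05. One who follows the sizing would use 0.0167. Both could say that they had followed the protocol, at thresholds that differ threefold.

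The undesignated cosinor parameters add to this. With MESOR and amplitude both available, the HRV hypothesis may mean three tests or six, and the article does not say which parameter carries the primary claim. The introduction says that the findings will indicate evidence-based programme options for clergy, so a false positive on a primary outcome would have consequences.

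**Working it through.** **1. Reproduce the HRV sample size.** Inputs from Power analysis: effect size 0.50, power 80%, alpha 0.0167, loss 20%, design effect 1.3. A two-sided two-sample t-test needs 86 per arm. Inflating gives 86 x 1.3 / 0.8 = 139.75, so 140, as stated. The same calculation at alpha 0.05 needs 64 per arm, and 64 x 1.3 / 0.8 = 104. The figure of 140 therefore depends on the corrected alpha, and 0.05/3 = 0.0167 confirms its origin.

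**2. Closed-form error rates, all tests independent and all nulls true.** Benjamini-Hochberg (BH) on the three stress tests gives 5% in this case.

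- Three HRV tests at 0.05: 1 - 0.95^3 = 14.3%.
- Stress family plus three HRV tests at 0.05: 1 - 0.95^4 = 18.5%.
- Stress family plus six HRV tests (two parameters) at 0.05: 1 - 0.95^7 = 30.2%.
- Three HRV tests at 0.0167: 1 - 0.9833^3 = 4.9%.
- Stress family plus three HRV tests at 0.0167: 1 - 0.95 x 0.9833^3 = 9.7%.
- Stress family plus six HRV tests at 0.0167: 1 - 0.95 x 0.9833^6 = 14.1%.

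**3. Allow for correlation.** Two contrasts that share a control arm of equal size have correlation (1/n)/(2/n) = 0.5. The article gives no correlations between outcomes or between parameters, so these are assumed: stress with HRV 0 or 0.3, and MESOR with amplitude 0, 0.5 or 0.8. A simulation under the global null (300,000 runs per setting) gives the chance of at least one false primary claim, with stress under BH throughout:

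| HRV level | HRV parameters tested | Contrasts uncorrelated | Shared waitlist (0.5) |
|---|---|---|---|
| 0.05 each | one | 18.1-18.7% | 16.3-16.6% |
| 0.05 each | two | 25.1-30.1% | 22.4-27.0% |
| 0.0167 each | one | 9.4-9.7% | 8.8-8.9% |
| 0.0167 each | two | 12.4-14.0% | 11.2-13.0% |
| BH over the three HRV contrasts | one | 9.5-9.8% | 9.0-9.1% |

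For HRV alone, one parameter at 0.05, the rate is 12.5-14.4% across these settings. The stress family alone stays at 4.7-5.1%.

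**4. Pooling the two outcomes.** One BH family over six tests (three interventions, two outcomes) gives 4.7-5.0% under the global null. A Bonferroni split over six tests would use 0.05/6 = 0.00833. That needs 99 per arm before inflation, and 99 x 1.3 / 0.8 = 160.9, so 161 rather than 140.

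**The case against.** The strongest reply is that no sentence in the article sets HRV at 0.05. The only alpha given for HRV is 0.0167, so the authors evidently had a correction in mind. The article is condensed, it refers to a later finalization of the analysis plan, and that plan may hold the HRV rule and the choice of parameter. The analysis statistician is also to be blinded to allocation. This stands as far as it goes: the higher error rates are conditional on the literal reading. It does not remove the point. The article does state a multiplicity rule, limits it to one of two co-primaries, and so conflicts with its own sizing. That is more than a detail left for later.

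A reader might be tempted by four stronger readings, which the document does not support.

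- *The false-claim rate is 17-30%.* This takes 0.05 for HRV as settled. The 30% end also needs every test to be independent, whereas the article describes one waitlist arm and takes both parameters from the same fitted curve.
- *Both cosinor parameters will be tested as primary, or one will be picked after the results are seen.* The article says neither. It only leaves them unranked.
- *Heart rate is a rival primary endpoint.* The abstract does say "The primary outcomes for this study are self-reported symptoms of stress and heart rate at week 12", but the Heart rate section explains that the ECG recording is used to calculate HRV and fixes RMSSD as the index. This is shorthand.
- *The plan breaches a 5% study-wide limit.* No such limit is stated. The 0.0167 treats each outcome as its own family of three, and BH targets the false discovery rate, so its 5% family-wise rate holds only when all nulls are true. How far to correct across two outcomes is a design choice.

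**Conclusion.** The point holds as an inconsistency between stated rules, together with an undesignated primary parameter. HRV is sized for a three-way correction that the analysis text gives only to stress.

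Its size depends on the reading. On the literal one (HRV at 0.05), a false HRV claim has a chance of about 13-14% with one parameter, and any false primary claim about 16-19%. With two parameters and a shared waitlist, the latter is about 22-27%. On the reading favoured by the sizing (HRV at 0.0167), the rate over both co-primaries is about 9-10% with one parameter and 11-14% with two.

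These figures assume two-sided tests (which reproduce the sample size), all nulls true, equal arms for the 0.5 correlation, and the other correlations listed above. They also count success on either outcome as a primary claim, as the separately numbered hypotheses suggest. If success required both outcomes, there would be no inflation across outcomes, but the article states no such rule.

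**What to change.** In the Data analysis section, extend the correction to HRV: apply BH to the three HRV contrasts, as for stress, or use the Bonferroni level of 0.0167 from the Power analysis section. Name one cosinor parameter of RMSSD as the primary HRV endpoint and make the other exploratory. Record both choices before unblinding.

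The cost is wording, plus a stricter HRV threshold than 0.05. The planned 140 per arm already assumes that threshold. BH rejects whatever Bonferroni rejects, so using it would not reduce the planned power.

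This change brings the HRV family to about 5%. It leaves the rate over both outcomes at about 9-10%. Pooling both co-primaries into one family would bring that to about 5% under the global null, but this is optional and a matter of judgement: the HRV sizing did not assume it (161 per arm for Bonferroni over six tests), and data collection has ended, so numbers cannot be raised. Requiring success on both outcomes would change the hypotheses and goes beyond a clarification.
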